### Assessments

#### Outcome assessments

Outcome measures refer to the assessments that will be conducted both before and after intervention. The evaluation timepoints are:

$${T}_{pre}$$ at randomization, before intervention.

$${T}_{post}$$ at the end of the intervention.

(See the SPIRIT diagram in Table 1 for details).

Trained clinical/research staff neurologists, neuropsychologists, neurophysiologists, therapists, and radiologists will perform the assessments and will be blind to the participant intervention allocation except for recruiting neurologists who are not blinded and do not participate to the assessment. Data will be recorded in an ad hoc Case Report Form (CRF; details in Data collection and management section).

#### Primary

Changes from pre- $$({T}_{pre})$$ to post- $$({T}_{post})$$ treatment in GRASSP somatosensory scores of bilateral arms (12 is the maximum score for each side, equal to physiological condition) [32] are the primary outcome measure of the trial. Those changes will be computed assessing the difference between $${T}_{post}$$ and $${T}_{pre}$$ scores, or by computing the effectiveness, defined as the ratio between $${T}_{post}$$-$${T}_{pre}$$ difference and the maximum possible improvement for that specific scale, expressed in percentage.

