### Sample size

The sample size was calculated on the hypothesis that experimental intervention (BCI-MI training) is superior in improving the primary outcome measure. Based on preliminary findings in the Upper Extremity Motor Scores (UEMS) from the International Standards for Neurological Classification of SCI (ISNCSCI) ASIA Impairment Scale (AIS) [35] in experimental vs control condition, alpha level at 0.05, statistical power at 80%, and one-tailed t-test, 15 participants per group (Control-MI and BCI-MI) are needed. The analysis was performed using the statistical software STATISTICA 8.0 (Stat Soft. Inc. 1984–2007, USA) according to the algorithm implemented in the tool Power Analysis/Sample Size Calculation.

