### Statistical analysis

#### Primary analyses

Baseline characteristics will be described by summary statistics for each group (experimental and control intervention). Differences between groups at baseline $${T}_{pre}$$ will be tested to check that the groups do not differ statistically at baseline.

The primary analysis will be performed in per protocol (PP) population on GRASSP somatosensory score changes between $${T}_{pre}$$ and $${T}_{post}$$. The PP will include all randomized participants who will perform (minimum) 12 training sessions. T-test or Wilcoxon Mann–Whitney rank test for independent groups will be used to compare continuous and discrete outcome measures respectively. Statistical significance will be assessed by two-tailed test.

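### The primary outcome has two alternative definitions and two candidate tests, with no rule for choosing among them

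*Protocol article*

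**What the plan says.** The Primary section (under Assessments) makes pre-to-post change in the GRASSP somatosensory score of both arms the primary outcome. The ceiling is given per arm: "12 is the maximum score for each side, equal to physiological condition". The change is then defined twice. The first definition is the raw change: "Those changes will be computed assessing the difference between" the T_post and T_pre scores. The second follows after the word or: "scores, or by computing the effectiveness, defined as the ratio between" the T_post minus T_pre "difference and the maximum possible improvement for that specific scale, expressed in percentage". The section gives no order of preference, no fallback and no formula for the denominator.

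The Primary analyses section does not settle the matter: "The primary analysis will be performed in per protocol (PP) population on GRASSP somatosensory score changes between" T_pre and T_post. On the test, it says that a t-test or a Wilcoxon Mann-Whitney "rank test for independent groups will be used to compare continuous and discrete outcome measures respectively". It does not say whether the primary outcome counts as continuous or discrete. It adds: "Statistical significance will be assessed by two-tailed test".

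Two other sections bear on the ceiling. The inclusion criteria limit impairment only through predicted motor recovery (UEMS) and set no limit on baseline somatosensory score. The randomization section stratifies the GRASSP somatosensory score at 8, and its upper stratum has no upper bound.

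**The concern.** A confirmatory comparison needs one variable and one test, fixed in advance. Here the document supports two variables and two tests, and each of the four combinations could be reported as the planned primary analysis. If the choice were made with outcome data in view, the 5% error rate would no longer hold. Even without any such selection, the versions can lead to different conclusions, so the headline result of a 30-person trial could depend on a decision that the document leaves open.

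The two versions may also measure different things. A raw difference treats a point gained anywhere on the scale alike. A percentage of the room left to improve gives most weight to participants who start near normal, and it has no value for someone with no room left.

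**Working it through.** **Inputs.** From the Primary section: maximum 12 per side, hence 24 if the two sides are summed. From Sample size: 15 per group and alpha 0.05. From Primary analyses: two-tailed testing and the choice of t-test or rank test. The article gives no GRASSP means, SDs or baseline distribution, so the simulation distributions below are assumptions.

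**The plan's own figure.** The sample size statement ("alpha level at 0.05, statistical power at 80%, and one-tailed t-test, 15 participants per group (Control-MI and BCI-MI) are needed") cannot be reproduced, because no effect size or SD is given. It can only be inverted: a one-sided t-test at 0.05 with 80% power and 15 per group implies a standardized difference of 0.93. It rests on UEMS data, so it does not show which version of the GRASSP change was intended.

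**Step 1: denominator read as maximum minus T_pre.** Effectiveness = 100 × (T_post − T_pre) / (maximum − T_pre).

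Per side (maximum 12):
- 2 to 4: difference 2; 100 × 2/10 = 20%
- 10 to 12: difference 2; 100 × 2/2 = 100%
- 11 to 12: difference 1; 100 × 1/1 = 100%
- 12 to 12: difference 0; 0/0, undefined
- 12 to 11: difference −1; −1/0, undefined

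On the 0-24 total, a one-point gain equals 100/(24 − T_pre): 100/24 = 4.2% from 0, 100/6 = 16.7% from 18, and 100/1 = 100% from 23. Participants are ordered differently from the raw difference, so these are different endpoints.

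**Step 2: denominator read as the fixed range.** Per side, effectiveness = 100 × difference/12. The same five cases give 16.7%, 16.7%, 8.3%, 0% and −8.3%. This is always defined and is a constant multiple of the difference, so any given test returns the same p-value for both versions.

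**Step 3: illustrative simulation under the Step 1 reading.** The set-up was 15 per arm and 4,000 runs per scenario. Baseline was uniform, or skewed high as maximum × Beta(3, 1.5). Each participant recovered a normally distributed share of the remaining room (mean 0.30, SD 0.25), plus noise of SD 1.2, rounded and kept within the scale. Participants at ceiling have no effectiveness value. All tests were two-sided at 0.05. Null rejection rates:

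| Scale, baseline | Each single option | Better of rank-on-difference and t-on-effectiveness | Best of all four pairs | Mean number at ceiling (of 30) |
|---|---|---|---|---|
| 0-24, uniform | 4.1-4.9% | 7.3% | 9.2% | 1.2 |
| 0-24, high | 4.4-4.5% | 7.1% | 8.9% | 0.4 |
| 0-12, uniform | 4.7-5.4% | 8.2% | 10.0% | 2.3 |
| 0-12, high | 4.8-5.2% | 8.1% | 9.5% | 1.1 |

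Each option alone is close to 5%; the excess comes only from choosing among them. With a true effect (recovered share raised by 0.25 in one arm), rank-on-difference and t-on-effectiveness disagreed on significance in 30%, 27%, 22% and 17% of trials, in the order of the table.

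**Step 4: the test choice alone.** If only the raw difference is used (or effectiveness is a mere rescaling) but the test stays free, a null simulation of the same kind gives about 6%. Most of the excess therefore needs the Step 1 reading.

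**The case against.** The strongest reply is that this is a condensed article and that details of derivation belong in a full protocol or analysis plan that is not shown. That covers much, including the handling of participants at ceiling and how the two sides are combined. It does not cover the main point: the article does not leave the metric out but states two with no rule. Nor does the mention of SAP under Secondary analyses defer the choice, because the abbreviation list defines SAP as a university.

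Other parts of the reply stand and limit what can be said:
- A reader might infer that the percentage is simply undefined at the scale ceiling. That holds only if the denominator is maximum minus T_pre. The wording, which refers to the specific scale, also fits a constant. The baseline-dependent reading is the more natural one, since a constant would make the second definition redundant, but the document does not state it.
- A reader might infer that the choice of metric dictates the test. The article ties the test to continuous or discrete type and links neither type to either version. A ratio of bounded integers is itself discrete.
- A reader might fear that arms will be analysed as 60 independent units. Nothing proposes this; the outcome is described for both arms, and the analysis set consists of randomized participants.
- The inflated error rates assume that the favourable result is picked after the data are seen. Nothing says the team intends that.

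**Conclusion.** The point holds: the primary change has two definitions and two candidate tests, and neither section chooses. This follows from the text and needs no assumption.

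Its size is conditional. An error rate of about 7-8% (about 9-10% with the test also free) requires selection after seeing the data, a denominator of maximum minus T_pre, and score distributions like those assumed. It shows what the open wording permits and is not the trial's actual error rate. Under the fixed-range reading only the open test matters, at about 6%. The ceiling problem is possible because eligibility does not exclude a normal somatosensory score. How many participants it would touch is unknown; the assumed baselines gave 0.4 to 2.3 of 30.

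**What to change.** Before unblinding, amend the Primary and Primary analyses sections to state:

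1. The primary variable is the patient-level bilateral GRASSP somatosensory total (0-24).
2. T_post is compared between groups by ANCOVA adjusted for T_pre, two-sided at 0.05. This replaces the open choice of t-test or rank test for the primary outcome. With T_pre in the model, using T_post or the raw change as the response gives the same treatment estimate, so that choice disappears too.
3. Effectiveness, with its denominator written as a formula, and the per-side scores are supportive.
4. Participants at 24/24 at T_pre stay in the primary analysis with their raw scores.

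The cost is a short amendment through the route described under Trial monitoring, and a matching update of the registered outcome definition if it carries the same alternative. Both scores are already collected, so no new data are needed.

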#### Secondary

The secondary outcome measures are the changes from pre- $$({T}_{pre})$$ to post- $$({T}_{post})$$ of the following fields and assessment scales:muscle strength: the GRASSP motor score of bilateral arms that ranges from 0 (maximum impairment) to 50 (normal) for each side [32]; the UEMS and the Lower Limb Motor Score (LEMS) from the ISNCSCI AIS evaluation for the residual strength assessment in upper and lower limb segments, it ranges from 0 to 25 for each arm and leg [35]; the arm will be considered as dominant and non-dominant according to the results of the Edinburgh Handedness Inventory [37];muscle tone: the Modified Ashworth Scale (MAS) for the muscle tone assessment of upper and lower limbs [38] ranging from 0 (absence of augmented muscle tone) to 4 (non-reducible spasticity); the Penn Spasm Frequency Scale (PSFS) for the self-assessment of upper and lower limb spasms frequency (ranging from 0, absence of spasms, to 4, more than 10 spasm each hour) and severity (ranging from 1, mild, to 3, severe) [39];pain: the International SCI Pain Basic Dataset (ISCIBPDS) for pain assessment; a pain-intensity, rating from 0 to 10, quantifies pain impact on activities daily living, humour, and sleep functions [40];functional ability: the GRASSP prehension ability ranging from 0 to 12 for each side and prehension execution ranging from 0 to 20 for each side; the Spinal Cord Injury Independence Measure (SCIM) self-care section score ranges from 0 (maximum impairment) to 20 (independence) [33].

Other specified secondary outcome measures will be extracted from neurophysiological, neuroimaging, neuropsychological and user experience assessments (see below).

##### Neurophysiological assessment

This includes:the Motor Evoked Potentials (MEPs) to evaluate the changes in corticospinal tract integrity. MEPs will be recorded from the bilateral Abductor Digiti Minimi (ADM, for the upper limbs) and Abductor Hallucis (AH, for the lower limbs) muscles by following the methodology reported in [41]. In brief, transcranial magnetic stimulation will be delivered in single stimuli at maximum output stimulator (5 stimuli for each side) and electromyographical (EMG) activity will be recorded from ADM/AH muscle bilaterally, if allowed during voluntary contraction. EMG traces will be superimposed to determine MEP latency. Peripheral motor conduction time (PMCT) will be obtained by recording Compound Muscle Action Potentials (CMAP) and F-waves from ulnar and tibial nerves (upper and lower limbs respectively) bilaterally. PMCT will be calculated as (CMAP latency + F wave latency – 1)/2. Central motor conduction time will be calculated as MEP latency – PMCT.the Somatosensory Evoked Potentials (SSEPs) to evaluate the ascending sensory pathways. SSEPs will be recorded according to clinical standards, as briefly reported below. Electrical stimulation will be delivered to the median (upper limbs) and tibial (lower limbs) nerves (at motor threshold or 4 times sensory threshold, when applicable). Responses will be recorded at the Erb point (N9), cervical cord (N13) and scalp (N20) for the upper limbs and at lumbar cord (N22) and scalp (P40) for the lower limbs via bipolar derivations by means of surface electrodes, bandpass filtered between 30–3000 Hz and averaged (at least 2 averaged responses of minimum 100 stimuli each, according to patients’ collaboration and recording conditions – signal to noise ratio) [42].the high-density EEG recordings to evaluate the neurophysiological substrates of the experimental intervention efficacy at $${T}_{pre}$$ and $${T}_{post}$$ and to identify offline the BCI control features for each participant, see Intervention - *BCI-assisted motor imagery training (experimental intervention)* section. All participants will be comfortably seated in an armchair (or directly on their wheelchair) in a dimly lit room (laboratory) with their upper limbs resting on a pillow. EEG data will be collected from 61 positions, assembled on an active electrode cap (g.GAMMAcap equipped with g.SCARABEO active electrodes, g.tec medical engineering GmbH Austria) according to an extension of the 10–20 International System; ground: left mastoid, reference: auricular lobes. EMG data will be collected from the extensor digitorum and flexor digitorum superficialis muscles of both upper limbs and from the extensor indicis proprius of the dominant arm. Biosignals will be recorded and amplified by the g.HIamp amplifier (g.tec medical engineering GmbH Austria).Each recording session will consist of (i) four minutes of EEG recording at rest (closed and opened eyes), (ii) four runs during the MI tasks (MI session), (iii) four runs during the finger tapping task (FT session) whether the participant can perform the task.Each MI session will consist of 4 runs, 40 trials each. Each run will consist of 2 tasks: i) hand kinesthetic MI [43] task which will consist of either hand closing or opening, (identical to those performed during the intervention training) and it will involve simultaneously both hands and, ii) rest. Each run will include 20±1 MI trials and 20±1 rest trials in a randomized order. At the beginning of the session, participants will be allowed to attempt the execution of the motor tasks with both hands (whenever possible) for a limited number of trials to facilitate task comprehension and the rehearsal of sensorimotor sensations evoked by the actual execution during MI performance. Instructions for the participant will be “Imagine to close/open your hands in first person by trying to feel the sensations as if you were actually performing the movement”. Visual cues will be presented as visual representation of two hands on a black screen, dimly illuminated for 3s, then both hands will be lit-up and participants will be instructed to imagine the hands movement for 4s, then both hands will disappear from the screen when the trial ends. In rest trials, both dimly lit hands will be presented to the participants for the whole trial duration (7s) after which a black screen will appear. Each trial will be contextually defined by a written instruction on the screen (“rest” “image hands closing” “image hands opening”) and verbal cues from the researcher. During the intertrial interval, participants will be confronted with a black screen. The total trial duration will be 8.5s with an intertrial interval of 1.5s. EEG and EMG data will be recorded and sampled at 256 Hz.Changes of the motor relevant oscillatory activity will be measured as significant changes in the Power Spectral Density (PSD) maps (details in [30]). The PSD analysis will be performed offline on the high-density EEG data recorded at $${T}_{pre}$$ and $${T}_{post}$$ to describe the differences between the BCI-MI and Control-MI conditions. Changes of the brain networks between $${T}_{pre}$$ and $${T}_{post}$$ will be also measured as significant changes in the EEG-derived functional connectivity under rest (resting state) and task conditions (MI with both hands) [44–46].As for the FT, the session will consist of 4 runs, 30 trials each. In each trial the participant will attempt the execution of the index finger tapping movement with his dominant hand assessed as in [37] . Before the experiment, the participant will have a few minutes to familiarize themselves with the task. Instructions for the participant will be “Attempt to execute the index finger tapping as quickly and widely as you can”. Visual cues will be presented to the participant: a fixation cross lasting 2 s will forerun the beginning of each trial. Participants will be instructed to perform the finger tapping when a green circle will appear on the screen (stimulus duration of 0.8 s) and rest during the black screen (resting duration randomly set in the range from 3 s to 7 s). EEG and EMG data will be recorded and sampled at 1024 Hz. EEG data will be pre-processed and aligned according to the movement onset extracted by the EMG activity recorded over the extensor indicis proprius muscle and analysed to extract the movement related cortical potentials, well-known as descriptors of the impairment in SCI population [47].

##### Neuroimaging assessment

The neuroimaging protocol is derived from Cohen-Adad et al. [48]. For registration purposes, T_1_- and T_2_-weighted volumetric images will be acquired to assess lesions and to compute the spinal cord Cross-Sectional Area (CSA) with a sagittal orientation along the spinal cord. Protocol will be based respectively on MPRAGE, 1^3^ mm^3^ voxels, FOV 320 × 260 mm^2^, TE/TI/TR = 3.72/1000/2000 ms, and SPACE, 0.8^3^ mm^3^ voxels, FOV 256 × 256 mm^2^, TE/TR = 120/1500 ms. Magnetization Transfer (MT) imaging will be performed to compute MT parameters, with Gradient Echo scanning, pseudo-axial slices oriented transversally to the spinal cord, 0.9 × 0.9x5 mm^3^ voxels, FOV 230 × 230 mm^2^. Multi-Gradient-echo images will be collected pseudo-axially to compute grey matter and white matter CSA with 0.9 × 0.9x5 mm^3^ voxels, FOV 224 × 224 mm^2^, TE_min_/TR = 14/600 ms, 3 combined echoes. Diffusion-weighted images will be acquired pseudo-axially to compute diffusion metrics, exploiting an inner-excitation spin-echo EPI sequence, 0.9 × 0.9x5 mm^3^ voxels, FOV 86 × 32 mm^2^, TE/TR = 62/3600 ms, b-values 0 s/mm^2^ (6 scans) and 550, 1000 s/mm^2^ along 63 isotropic directions.

All scans will be performed at FSL Neuroimaging Unit on a high-performance 3 T scanner (Siemens Magnetom Prisma) equipped with a 64-channel head and neck coil and a 32-channel spine array, after 2^nd^ order shimming where appropriate.

Scans will be collected in both experimental and control groups at $${T}_{pre}$$ and $${T}_{post}$$ and will allow comprehensive characterization of lesion features and of tissue microstructural integrity.

##### Neuropsychological and user experience assessment

The Neuropsychological assessment at $${T}_{pre}$$ and $${T}_{post}$$ includes the Trail Making Test (TMT) [49], the Test for Attentional Performance (TAP) [50] considering alertness, Go/no Go and working memory subtests, the Stroop Color and Word Test (SCWT) [51] to assess executive function and cognitive flexibility, the Beck Depression Inventory II (BDI-II) [52] to investigate the presence and severity of depression symptoms and the State Trait Anxiety Inventory (STAI) [53] to assess state and trait anxiety. The assessment also includes the Rubber Hand Illusion task (RHI) [54], a paradigm to assess the illusory ownership of a fake hand as part the body following synchronous tactile stimulation over a visible rubber hand and the hidden real hand of the subject, and the Cambridge Depersonalization Scale (CDS) [55] which is a scale used to assess the frequency and duration of depersonalization symptoms.

Finally, the user experience assessment of the technology-based training [56] will include:at each single training session: before starting an adapted version of the Questionnaire for Current Motivation (QCM) [57] to evaluate the motivation and the Visual Analog Scale (VAS) [58] ranges from 0, “very bad mood”, to 10, “very good mood” to monitor the patient’s mood; after the session the VAS will be used for evaluating the satisfaction defined as “freedom from discomfort and positive attitudes toward the use of the product”: it ranges from 0 “not satisfied” 10 “absolutely satisfied;at the first and last training session: the National Aeronautics and Space Administration Task Load Index (NASA-TLX) [59] for the workload related to the training;at the end of last training session: the System Usability Scale (SUS) [60] for usability, acceptability and satisfaction of technology evaluation.

### Randomization procedure and methods

The random allocation sequence of participants to experimental (BCI-MI training) or control (Control-MI training) intervention groups will be generated by using Matlab (The MathWorks Inc, Natick, Massachusetts, USA, release 2019a).

The randomization sequence will be stratified by age (2 categories: ≤ 50 years old and > 50 years old) [61] and by GRASSP somatosensory scores (2 categories: ≤ 8 and > 8). A 1:1 allocation ratio will be used. For each stratum, the sequence will include 30 random allocations. The allocation sequence is securely stored at FSL. Randomization of participants will stop after randomization of the 30th participant in the study by summing participants in all strata.

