## Methods/design

A total cohort of 30 participants will be enrolled and randomized in a single centre, single blind RCT to investigate the efficacy of BCI-MI training for hand movements, delivered during the subacute phase of SCI (hospitalization period). The primary and secondary outcome measures collected from participants assigned to BCI-MI training will be compared with those of participants who receive an equivalent dose of MI training without BCI support (Control-MI).

All procedures conducted in this trial follow national institutional ethical standards and the Helsinki Declaration. The study protocol and related procedures were approved by the institutional review board: the Independent Ethical Committee of the Fondazione Santa Lucia (FSL), I.R.C.C.S., Rome, Italy (protocol CE/PROG.884 15-12-2020). The trial was registered on the clinicaltrials.gov in 05-12-2022 (trial registration number: NCT05637775).

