### Intervention

#### Dosage of intervention training

Both BCI-MI and Control-MI training will be completed in 12 weeks with a weekly frequency of 3 sessions per week, lasting 45 min. Treatment adherence is set at 12 of the 36 intervention training sessions. We do not expect the BCI-MI and Control-MI interventions to cause adverse effects (non-invasive procedure; no drug-administration; no adverse events [30]) and both intervention deliveries will be under the care of SCI specialized personnel (physiotherapists, neurophysiology technician experts in patient EEG recordings). To monitor any possible deviation from the intervention training protocols (e.g., missing sessions for intervening illness), a report form for each participant will be compiled at each planned training session by the training personnel and it will be part of the CRF (CRF- Training section; details in Data collection and management section). The study interventions are conceived as add-on to the standard rehabilitation care (treatment as usual; TAU), and both groups will receive the same dosage of TAU and add-on training. To ensure comparability between and within group, TAU will be delivered according to an equal intensive regimen for both groups. The intensive regimen includes neuromotor physiotherapy sessions of 40 min each, twice a day, except on Saturdays, when it is once a day, for 6 days a week.

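### The 15 per group stated as needed for 80% power equals the number randomised, while the primary analysis can only use fewer: no visible margin for losses

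*Protocol article*

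**What the plan says.** Sample size: "alpha level at 0.05, statistical power at 80%, and one-tailed t-test, 15 participants per group (Control-MI and BCI-MI) are needed". The section mentions no allowance for losses and prints neither an effect size nor a standard deviation; the effect is attributed to preliminary UEMS findings.

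Methods/design: "A total cohort of 30 participants will be enrolled and randomized in a single centre, single blind RCT".

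Randomization procedure and methods: "A 1:1 allocation ratio will be used", and "Randomization of participants will stop after randomization of the 30th participant in the study by summing participants in all strata". The count that closes the trial is of participants randomised, not of participants who can be analysed.

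Primary analyses: the primary comparison is per protocol, on the change in GRASSP somatosensory score between the two assessments. "The PP will include all randomized participants who will perform (minimum) 12 training sessions". Significance is assessed two-tailed.

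Dosage of intervention training: adherence is set at 12 of 36 sessions over 12 weeks. Deviations are to be recorded on a form, with "missing sessions for intervening illness" given as an example.

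**The concern.** The number that the power calculation requires (15 per group) and the number randomised (30 in all) are the same, yet the primary analysis set is defined by a rule that removes randomised participants. There are two routes out of that set: fewer than 12 sessions, or no post-intervention score from which to form a change. Neither route can be offset by the stop rule, which counts randomisations.

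At stake is how the result is read. If the trial is null, readers will set it against 80% power. That figure describes an analysis of all 30 participants, and the analysis actually carried out may hold fewer. This differs from the question of whether a per-protocol set is biased, because a missing post-intervention score reduces the number under any analysis set that uses the observed change. It also differs from the mismatch between a one-tailed calculation and a two-tailed test, because it remains on the plan's own one-tailed terms.

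**Working it through.** **Inputs from the article.** Alpha 0.05, power 80%, one-tailed t-test and 15 per group (Sample size); 30 randomised at 1:1 (Randomization procedure and methods); two-tailed test and a per-protocol set needing at least 12 sessions (Primary analyses).

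**Input not given.** The standardised difference d. The 15 per group therefore cannot be reproduced forwards, and d is back-solved from it.

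**Formula.** For analysed group sizes n1 and n2:
- degrees of freedom = n1 + n2 - 2
- noncentrality = d / sqrt(1/n1 + 1/n2)
- one-tailed power = P(noncentral t > t quantile at 0.95)
- two-tailed power uses the 0.975 quantile and both tails.

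**Step 1: which d fits the statement that 15 are needed.** Power is exactly 80% at 15+15 when d = 0.931 (noncentrality 0.931 / sqrt(2/15) = 2.55, 28 degrees of freedom). Power is exactly 80% at 14+14 when d = 0.965. So 15 per group is the smallest sufficient number for d from 0.931 to just under 0.965.

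**Step 2: power as participants are lost.** Each range runs from d = 0.931 to d = 0.965. Losses are spread as evenly as possible over the arms.

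| Analysed | Lost of 30 | One-tailed power | Two-tailed power |
|---|---|---|---|
| 15+15 | 0 | 80.0-82.5% | 69.2-72.3% |
| 15+14 | 1 | 78.7-81.2% | 67.5-70.7% |
| 14+14 | 2 | 77.4-80.0% | 65.9-69.1% |
| 14+13 | 3 (10%) | 76.0-78.6% | 64.2-67.3% |
| 12+12 | 6 (20%) | 71.4-74.1% | 58.7-61.8% |
| 10+10 | 10 (33%) | 64.0-66.7% | 50.4-53.3% |

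One-tailed, a single loss may or may not take power below 80%, depending on the unreported d. Two losses bring it to 80% at best, at the very top of the range. From three losses it is clearly below 80% throughout. Uneven losses are no better: 15+12 gives 75.6-78.2%.

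**Step 3: how likely losses are.** The article gives no rate, so two illustrative rates are used, with independent losses.
- Chance that all 30 stay analysable: 0.95^30 = 21% at a 5% risk each; 0.90^30 = 4% at 10%.
- Chance of three or more losses is 1 minus the chance of zero, one or two. At 5%: 1 - (0.215 + 30 x 0.05 x 0.95^29 + 435 x 0.05^2 x 0.95^28) = 1 - (0.215 + 0.339 + 0.259) = 19%. At 10%: 1 - (0.042 + 0.141 + 0.228) = 59%.

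**Limits of the check.** It assumes that the 30 split 15 and 15. With a separate list of 30 allocations for each of four strata and one overall stop, that is not guaranteed. An 18/12 split with no loss gives 78.6-81.1% one-tailed.

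**The case against.** **Losses may be few.** Participants are inpatients, and a participant can miss 24 of 36 sessions and still be analysed. The remark about missed sessions concerns the recording of deviations; it does not predict exclusions. This stands. It limits the likely size of the problem and makes every loss rate above an assumption, but the plan still shows no allowance, and a missing post-intervention score is a second route of loss that the session threshold does not affect.

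**The article is a summary.** An attrition assumption could sit in the full protocol, and its absence here alone would be no finding. That is right, and the point does not rest on absence. It rests on the printed equality of the number needed and the number randomised. If 15 already contained an allowance, the number needed for analysis would be below 15, and "15 participants per group (Control-MI and BCI-MI) are needed" would not mean what it appears to mean. Either way the sentence needs to say which number it is.

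**Two stronger readings are tempting.** A reader might infer that the stated power holds only with zero attrition. The document does not support that: n is rounded up to a whole number and d is not printed, so near d = 0.965 one loss leaves about 81% and two about 80%. The first loss breaks the stated head count, not necessarily the 80%. A reader might also infer that nobody is replaced. That is a reasonable inference from the stop rule, but no sentence says it.

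**Other problems are larger.** The one-tailed versus two-tailed conflict costs about 10 points with nobody lost, against about 4 for three losses. This stands too, and it is why restated power must use the planned test.

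**Conclusion.** The point holds as a lack of visible margin. On the plan's own one-tailed terms, power is 80-82.5% with all 30 analysed, 76-79% with 14+13 and 71-74% with 12+12. For the planned two-tailed test the figures are 69-72%, 64-67% and 59-62%. These rest on an effect back-solved from 15 per group, an even split between arms, an exact t calculation and assumed losses. They also take the UEMS-based effect as valid for the GRASSP somatosensory score, which the article does not show. The consequence is an overstated power figure; the estimate and the validity of the comparison are not affected by it. It should be corrected, but it does not undermine the trial.

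**What to change.** 1. In Sample size, state that 15 per group means participants analysed (or, if an allowance is already included, say so and give the number needed for analysis).
2. In the same place, restate the power for 30 randomised under a stated, plausible loss rate, computed for the test actually planned. On the assumed effect, and if the two-tailed test is kept, that is about 64-67% with 10% not analysed and 59-62% with 20%. One-tailed figures should not be printed beside a two-tailed test.
3. In Randomization procedure and methods, say whether participants who stop are replaced. The text should record the sponsor's actual rule, not an inference from the stop rule.

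If the primary set were changed to all randomised participants with a post-intervention score, whatever their attendance, the loss rate in step 2 would be that for missing scores only.

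The cost is wording in two sections and a less favourable stated power. No additional enrolment is required.
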